### Missing data methods

If missing data are higher than 5% in any of the matching variables or moderators, then multiple imputation will be used to handle missing data [53]. Missing data rules for within measures will be followed where available (e.g., within the PHQ-8). Counts of children missing the outcome will be presented with reasons where possible, and tabulations of those who are missing the outcome will be created by the matching variables to explore whether there are any differences in characteristics between those with outcome data and those without.

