**Matching variables for propensity score**		
Prenatal attachment (Prenatal Attachment Inventory)	Continuous	[10, 11, 41]
Prenatal Depression (PHQ-9)	Continuous	[10, 11, 41, 42]
Prenatal Anxiety (GAD-7)	Continuous	As above
Ethnicity	Categorical	[10, 11, 30, 41, 43]
Socioeconomic position (financial security)	Continuous	[30, 42, 44–46]
Speaks English	Binary	[30, 46]
Immigration status (proportion of life spent in UK)	Continuous	[30, 47, 48]
Length of time in COVID lockdown	Continuous	[49]

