### Variables

The Directed Acyclic Graph (DAG) in Fig 2 identifies the confounding variables that will be used as matching variables in the propensity score [38, 39]. We will match on the 7 characteristics on the left-hand side of the graph (prenatal attachment, prenatal depression, prenatal anxiety, ethnicity, socioeconomic status, language status, and immigration status) to estimate the effect of treatment (IY-T) on the primary outcome (child social and emotional development).

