**Fig 2 pone.0291557.g002:**
[figure not shown]
Directed Acyclic Graph of associations between confounders, covariates, moderators, treatment exposure, and outcome. Notes: 1. SES = socioeconomic status. 2. The secondary outcome (children’s early years school skills) is not depicted here.

The justification for the selection of these variables is given in Table 2 below. Variables which affect program participation but not the outcomes should not be used in propensity score matching, as this increases the error in the estimated values [40]. Matching variables were therefore selected if they were thought to have an association with both uptake of treatment, and with the outcomes (child early years development), and there was evidence to suggest this was the case. See Table 2 for a summary of the evidence for using a matching variable, and the tested moderators of the effect. We have proposed that we will test the effects of four moderators: child age, programme delivery mode, family socioeconomic status, and ethnicity, however, this will only be possible if a sufficient sample size is reached.

All variables are obtained from the BiBBS baseline questionnaire, which takes place before the child is born (see https://borninbradford.github.io/datadict/bibbs/ for details).

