### Study limitations

There is a paucity of routinely collected data within the early years of a child’s life, which limited our choice of an outcome measure. Whilst the EYFSP is a well-timed measure and represents a construct of interest to this study, other measures relating to outcomes that IY-T aims to effect would have been beneficial (e.g. of parent-child bonding) [56]. Further, as collection of EYFSP data was paused during the COVID pandemic, there will inevitably be missing outcome data for a small number of children. However, it is worth noting that EYFSP and other routinely collected health and education outcome data is regularly used as the basis for most policy-making decisions and this study reflects real-world conditions.

A further limitation of this evaluation is that it will not consider the involvement of fathers and other co-parents in the IY-T groups. Whilst fathers and co-parents of children are eligible for both BiBBS and IY-T, the number of enrolled fathers and co-parents in both the cohort and IY-T is unlikely to be sufficient to conduct any meaningful analyses on these groups. Whilst it can be more challenging to recruit fathers to parenting research studies [57, 58], we acknowledge that much further research and efforts is needed on the involvement of fathers and co-parents in parenting interventions, and will aim to explore this in our process evaluation of IY-T.

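### The 5% imputation trigger is set variable by variable, while the propensity score needs every matching variable, so the share of families without a score is not capped near 5%

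*Protocol article*

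**What the plan says.** The Missing data methods section sets one rule for covariates: "If missing data are higher than 5% in any of the matching variables or moderators, then multiple imputation will be used". It adds that the scoring rules of individual instruments for missing items will be followed where they exist. It does not say what happens when no variable is above 5%, and it puts no limit on the share of families with at least one gap.

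The propensity score is built from several variables at once. The Variables section says "We will match on the 7 characteristics on the left-hand side of the graph"; Table 2 lists those seven and adds an eighth, "Length of time in COVID lockdown". The trigger also covers the four moderators, "child age, programme delivery mode, family socioeconomic status, and ethnicity", two of which (socioeconomic status and ethnicity) are already matching variables. On the source of the data, the protocol says "All variables are obtained from the BiBBS baseline questionnaire, which takes place before the child is born".

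The Sample size calculations section describes the sample as fixed by project capacity and recruitment. It gives 1336 participants (334 intervention, 1002 control) for 80% power on the primary outcome, with no stated allowance for missing data. The Included participants section says that the intention-to-treat analyses take in everyone who enrolled after an initial home visit.

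**The concern.** A per-variable threshold controls the wrong quantity. A propensity score can be computed only for a family with every matching variable observed, so what governs the loss is the share of families missing at least one of them. That share can be several times larger than the missingness of any single variable. If each variable stays at or below 5%, the rule does not call for imputation, and a family with one gap then has no score and cannot be matched.

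Two things are at stake:

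- **Precision.** The sample is fixed, so intervention families lost in this way cannot be made up by further recruitment.
- **The analysis set.** An enrolled family without a score drops out of the matched comparison, so the set analysed would no longer be all who enrolled.

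**Working it through.** **Inputs**

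- Trigger: more than 5% missing in any one variable (Missing data methods).
- Number of matching variables: k = 7 (Variables) or k = 8 (Table 2).
- Required sample: 1336, as 334 + 1002, for 80% power at an odds ratio of 1.5 with 1:3 allocation (Sample size calculations).
- Assumed, because not stated: two-sided alpha of 0.05.
- Assumed, because the protocol gives no missingness rates: m, the proportion missing per variable, set at the 5% limit and at lower values.

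**The plan's own figure.** The 1336 cannot be rebuilt exactly, because the outcome category probabilities are not given. Whitehead's proportional-odds formula with A = 3 is

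N = 3(A+1)²(1.96 + 0.8416)² / [A (ln 1.5)² (1 − Σp³)] = 764 / (1 − Σp³).

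A total of 1336 implies 1 − Σp³ = 764/1336 = 0.572, which corresponds to about 75% of children in the top category. That is plausible, so 80% power at 1336 is taken as the anchor below.

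**Share of families with at least one gap**

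- Complete overlap (the same families miss everything): m.
- Independent missingness: 1 − (1 − m)^k.
- No overlap: k × m.

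| k | m | Complete overlap | Independent | No overlap |
|---|---|---|---|---|
| 8 | 5% | 5% | 1 − 0.95⁸ = 33.7% | 40% |
| 7 | 5% | 5% | 1 − 0.95⁷ = 30.2% | 35% |
| 8 | 3% | 3% | 1 − 0.97⁸ = 21.6% | 24% |
| 8 | 2% | 2% | 1 − 0.98⁸ = 14.9% | 16% |
| 8 | 1% | 1% | 1 − 0.99⁸ = 7.7% | 8% |

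Imputation is not triggered in any of these rows, since 5% exactly is not above 5%.

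**Power if the sample before scoring is exactly 1336 and no lost control is replaced**

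Power = Φ(2.8016 × √(share retained) − 1.96)

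| Loss | Families left | Power |
|---|---|---|
| 0% | 1336 | 80% |
| 5% | 1269 | 78% |
| 14.9% | 1137 | 73% |
| 30.2% | 933 | 65% |
| 33.7% | 886 | 63% |
| 40% | 802 | 58% |

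**Power if lost controls are replaced in full.** Information is proportional to n₁n₂/(n₁ + n₂), which is 334 × 1002/1336 = 250.5 with no loss. With a 33.7% loss of intervention families only, about 221 face 1002 controls: 221 × 1002/1223 = 181.1. The ratio is 181.1/250.5 = 0.723, and power is Φ(2.8016 × √0.723 − 1.96) = 66%. Replacing controls therefore recovers little, because the intervention group is the limiting one.

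**The case against.** The strongest objections, and what stands of each:

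- **The fallback is inferred.** The section never mentions complete-case analysis or dropping families. This stands as a limit on the point. Even so, a threshold for imputing implies that below it there is no imputing, and a family with a missing covariate then has no score.
- **A reader might infer that about a third of families will be lost.** The documents do not support that. One third requires every variable at the ceiling, none above it, and independence across all of them; a single variable or moderator over 5% would trigger imputation. The variables are said to come from one questionnaire, so gaps may cluster in the same families and the loss would move towards 5%. Instrument-level scoring rules reduce gaps in the multi-item scales. Time in lockdown may be derived from dates and nearly complete (an assumption), which would leave the 7-variable figures.
- **1336 is the required number, not the pool before scoring.** This is correct. The pool size is not given, and lost controls may be replaceable. The power figures are conditional on this and are labelled so.
- **Intention to treat is defined by enrolment, not data completeness.** This is true of the definition, but an enrolled family that cannot be matched is still absent from the analysis.
- **A reader might infer that the families lost differ systematically from those kept.** The protocol gives no evidence either way, so no bias is claimed here.
- **A reader might infer that missing outcomes are badly handled, since the article plans only to count them and break them down by matching variable.** That does not hold as a finding. The Statistical methods section describes itself as a summary of an analysis plan to be preregistered, where weighting or sensitivity analyses would normally sit. The Study limitations section also expects few cases: "there will inevitably be missing outcome data for a small number of children".

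**Conclusion.** The concern holds as a defect in a rule that the protocol states, not as a missing detail. The trigger caps missingness per variable and leaves the joint share uncapped, although the joint share decides who can be scored and matched.

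At the 5% limit the possible loss runs from 5% to 40% with 8 variables and from 5% to 35% with 7. The independent-missingness scenarios within those ranges are 34% and 30%. At 2% per variable the independent figure for 8 variables is about 15%, so the gap does not depend wholly on the extreme case. Starting from exactly 1336 without replacement of controls, losses of 15% and 34% bring power to about 73% and 63%.

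The conclusion rests on three assumptions: families without a score are left out when imputation is not triggered, alpha is two-sided 0.05, and the missingness rates are those chosen for illustration. The actual loss could be small. The disagreement between 7 and 8 matching variables shifts the figures slightly and does not change the conclusion.

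**What to change.** Replace the per-variable trigger in one of two ways:

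- impute whenever the share of families missing any propensity-score variable exceeds a stated limit, for example 5%; or
- impute regardless of any threshold, which removes the dependence on a cut-off altogether.

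In either case, estimate the score and match within each imputed dataset, then combine the treatment estimates by Rubin's rules. If a threshold is kept, state what is done below it, and report how many enrolled families and potential controls lack a score.

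The cost is a few sentences in the SAP and extra computing time. The final analyses are planned for after August 2028, so there is time to settle this beforehand.

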### Robustness testing

Histograms of the distribution of the EYFSP variable will be created and the analysis be run with the EYFSP as both a categorical and continuous variable. The model fit and parameters will be compared between the models. The Stata user written command ‘overfit’ will be used to measure the amount of overfitting generated by each model.

### Software

Stata-17 will be used for data handling and analyses. The packages *teffects* and *psmatch2* will be used for matching, and *ologit* will be used for regression analysis.

### Economic analysis

The objectives for the economic analysis are to:

Estimate the cost of the intervention (including delivery and training to deliver IY-T),seek to combine these costs with the effectiveness data to inform a cost-consequence analysis, andto explore extrapolating the effectiveness data generated by this analysis to longer-term outcomes through an existing simulation model.

The costing analysis will seek to apply an existing framework for conducting micro-costing [54] in addition to previous costings conducted in a previous randomised trial of IY (the E-SEE study) [19]. Where possible, we will generate a cost per participant in each group, estimate the cost of the intervention, and who that cost falls upon. These costs will be reported alongside the effectiveness outcomes described in the ‘Outcome’ sections of this protocol to inform a cost-consequence analysis, including potential sub-group analysis stratified by socioeconomic status. Finally, by applying ongoing research mapping the EYFSP to the Strengths and Difficulties Questionnaire (SDQ) [Mooney et al., in preparation] to a life course dynamic microsimulation model [55] we will explore the extrapolation of findings of this study over the lifetime of the children who both receive IY-T and the matched control group.

### Pilot data

An interim profile of BiBBS for all pregnant women recruited between January 2016 and November 2019, with an expected due date between 1st April 2016 and 8th March 2020, indicated that the BiBBS cohort sample is representative of the Better Start Bradford pregnant population. Furthermore, a high proportion (85%) of BiBBS families had engaged in one or more of the Better Start Bradford interventions, including in IY-T [28]. This data demonstrates the feasibility of conducting the IY-toddler evaluation in a disadvantaged population.

### Process evaluation

A process evaluation will explore aspects of implementation fidelity including dose (number of sessions attended) and adherence (self-reported Group facilitator checklists). Parent and practitioner perspectives on the impact of IY-T, and barriers and facilitators to implementation will be explored. Fathers and other co-parents will be involved in the process evaluation where possible. The plans for this study will be specified in a separate process evaluation protocol.

### Data management

As per the BiBBS protocol, record matches for routine data linkage, including health, education and IY-T data will be validated based on NHS number plus multiple non-unique identifiers (e.g., surname, date of birth) where possible. Identifiable data is only accessible by a small number of the research team (not the authors of this study), and is only done for approved processes such as withdrawals; address updates etc. Data for evaluations is processed and fully anonymised before being shared with researchers. The central database, hosted by BTHFT, will store data obtained from all sources. Data from each source will be linked at the BiBBS person level and will be structured and maintained by BiBBS data managers as a long-term strategic store to service cohort data capture and analysis. The entire database schema and data will be backed up nightly. All data will be stored within the cohort-specific Relational Database Management System (RDBMS) and managed using Microsoft SQL Server 2018 Management Studio.

## Discussion

This quasi-experimental evaluation will establish the effectiveness (or not) of the IY-T programme on children’s social and emotional wellbeing and early years school skills two to four years post parent attendance in IY-T groups. It will provide a unique insight into the effects of the IY-T programme in an ethnically and socioeconomically diverse population. This study will harness the BiBBS cohort to enable links to routine data, allowing an exploration of the effects of IY-T on children’s EYFSP scores. The intervention is offered in a real-world context, in a setting where the intervention would exist whether we evaluated it or not. We will utilise an existing data set to conduct a quasi-experimental evaluation; hence it allows for a low-cost, efficient, and timely evaluation compared to a full RCT. The findings regarding intervention effectiveness of IY-T will be generalisable to other urban areas that are ethnically diverse with high levels of socioeconomic deprivation. They may also be generalisable beyond IY-T to other parenting programmes more widely, though this will depend on the contents and implementation of the individual programmes.

Beyond this study, it will be possible to follow the very long-term outcomes of the children whose parents have and have not received IY-T in the BiBBS cohort. Whilst this planned study aims to first examine the impact of IY-T on children’s social and emotional wellbeing and school skills at age 5, it will also eventually be possible to examine any impacts of IY-T into adolescence (e.g. through routine education data) and adulthood (e.g. through access to medical records to infer incidence of mental health problems). Again, this highlights the utility of a quasi-experimental study nested within an interventional cohort.

### Study limitations

There is a paucity of routinely collected data within the early years of a child’s life, which limited our choice of an outcome measure. Whilst the EYFSP is a well-timed measure and represents a construct of interest to this study, other measures relating to outcomes that IY-T aims to effect would have been beneficial (e.g. of parent-child bonding) [56]. Further, as collection of EYFSP data was paused during the COVID pandemic, there will inevitably be missing outcome data for a small number of children. However, it is worth noting that EYFSP and other routinely collected health and education outcome data is regularly used as the basis for most policy-making decisions and this study reflects real-world conditions.

A further limitation of this evaluation is that it will not consider the involvement of fathers and other co-parents in the IY-T groups. Whilst fathers and co-parents of children are eligible for both BiBBS and IY-T, the number of enrolled fathers and co-parents in both the cohort and IY-T is unlikely to be sufficient to conduct any meaningful analyses on these groups. Whilst it can be more challenging to recruit fathers to parenting research studies [57, 58], we acknowledge that much further research and efforts is needed on the involvement of fathers and co-parents in parenting interventions, and will aim to explore this in our process evaluation of IY-T.

## Conclusion

This study will contribute to the growing evidence base regarding the effectiveness of the IY-T programme [17–19], and more broadly, the literature regarding effectiveness of parenting education programmes in underserved communities [9, 12, 14, 21]. This quasi-experimental study will provide useful evidence for policy makers and commissioners regarding IY-T and parenting education programmes, and it may ultimately improve outcomes for children living in a disadvantaged area.
